### Clinical procedures

Study participants will have undergone the standard clinical assessment of ED patients with chest pain. This includes a triage history, routine initial observations of pulse, blood pressure, respiratory rate, oxygen saturation and the recording of a 12-lead ECG. Standard clinical practice dictates that routine blood sampling for the assessment of full blood count, urea and electrolytes and troponin is undertaken at presentation.

#### Baseline ECG

A baseline 12-lead ECG will be recorded in all patients with chest pain as part of standard clinical care. Patients identified by treating clinicians as having an ECG diagnostic of an ST-elevation myocardial infarction or evidence of new ischaemia (new T wave inversion >3 mm or ST depression >1 mm) will be ineligible.

#### Baseline blood sampling

All participants will have a blood sample taken for hs-troponin measurement on, or shortly after, ED arrival as part of the standard clinical assessment of patients with chest pain. No additional blood sampling is required for study purposes. All study centres have access to hs-troponin assays which already form part of standard care.

Given the pragmatic nature of the trial, ‘presentation’ blood sampling will be defined as the first blood sample taken after arrival in the ED. Blood sample results will not be delayed for trial purposes.

Standard laboratory reporting of hs-troponin results and other routine baseline blood tests will be used for both clinical assessment and for data collection purposes. At all sites this is through an electronic clinical record. Data from the laboratory system will be anonymously recorded within the case report form (CRF).

#### Repeat troponin tests

The default strategy will be existing rule-out strategies used in study centres (the control group). Therefore, a second hs-troponin test may be taken within these strategies so as not to delay routine clinical care. However, if allocation is to the LoDED strategy, clinicians will not be required to obtain the results of the second hs-troponin test and immediate discharge can occur.

#### Laboratory analysis

Clinical blood samples will be analysed locally in central hospital laboratories for the Elecsys hs-troponin T assay (Roche Diagnostics, 99th percentile 14 ng/L, coefficient of variation <10%, LoD 5 ng/L), Architect STAT high-sensitive troponin I (Abbott Diagnostics, 99th percentile cut-off of 26 ng/L, coefficient of variation 4%, LoD 2 ng/L) or Access hs-troponin I (Beckman Coulter, 99th percentile cut-off of 18 ng/L, coefficient of variation <10%, LoD 2 ng/L).^5 20^ Results will be made available to clinicians using laboratory reporting systems as per routine clinical care.

### Randomisation

After written consent has been obtained, participants will be randomised to be evaluated using either the existing rule-out strategy used in study centres (control) or the LoDED strategy (intervention) in a 1:1 ratio. The CTU, in conjunction with the study statistician, will provide web-based randomisation, stratified by centre and minimised by age and gender.

To randomise a participant, the recruiting doctor, ED nurse or research nurse will access the secure website and enter brief participant details (initials, date of birth, gender, study site). Once the randomisation process is complete, the computer screen will indicate which diagnostic strategy to follow, including details of the local rule-out strategy for control participants as a reminder for site staff. A printout of the allocation generated by the randomisation website will be taken and filed in the participant’s ED records.

### Trial interventions

Participants fulfilling the inclusion criteria will be randomised to be managed according to the existing local rule-out strategy (control) or the LoDED strategy (intervention).

#### Usual rule-out strategies (control)

Usual care varies between study sites but includes ECG on arrival and usually two hs-troponin tests. All sites take the first sample at presentation, but the minimum time delay between the two samples varies. The existing rule-out strategy in use at each study site will be documented at study commencement and filed in the relevant investigator site file.

#### LoDED strategy (intervention)

Participants randomised to the LoDED strategy will be eligible for discharge after a normal ECG and single hs-troponin test at presentation to the ED if the hs-troponin is below the LoD for the assay in use at the study centre.

Any participant not fulfilling this discharge criterion will revert to the existing rule-out strategy in use at that study site and have a second hs-troponin test after 1–6 hours as per usual care.

### Postintervention procedures

#### Clinical management

Once hs-troponin results are available (for either control or intervention pathways) the discharge decision will be entirely at the discretion of the treating clinician. Onward referral for outpatient investigation, such as chest pain clinics, will follow local guidance and will not be altered for trial purposes.

#### Participant advice

All participants discharged according to the LoDED strategy will be given a study-specific leaflet containing written information about the tests they have had during their stay and what to do should their chest pain returns, or if they have any concerns (online supplementary material). Feedback will be sought during the study on the content of this information leaflet and its wording refined for patient use if the LoDED strategy is adopted clinically (integrated qualitative study).

10.1136/bmjopen-2018-025339.supp1Supplementary file 1

#### Patient satisfaction survey and EQ-5D

All participants, irrespective of group allocation, with the exception of those admitted to an inpatient ward bed for further clinical management, will be asked to complete a bespoke written patient satisfaction questionnaire on discharge from the ED (or ED observation ward; EDOU) to compare treatment satisfaction between the two study groups.^19^

Participants with an initial hs-troponin below the LoD (irrespective of group allocation) will also be asked to complete a baseline EQ-5D health status questionnaire on ED/EDOU discharge, repeated at 30 days.^24^

### Outcomes

#### Primary outcome

The primary outcome is successful early discharge, defined as discharge from hospital within 4 hours of ED arrival, without MACE occurring within 30 days.

The safety endpoint of MACE occurring within 30 days, included within the primary outcome, will be defined as cardiac death, AMI or emergency revascularisation occurring within 30 days of ED attendance (including the index presentation). AMI will be defined according to the universal definition, which states that a rise and/or fall of troponin above the 99th percentile value confirms the diagnosis.^25^ A significant rise and/or fall will be defined as an absolute change in troponin over time of at least half the 99th percentile value of the assay in clinical use.^26^

#### Secondary outcomes

Secondary outcomes will include: length of ED/EDOU stay, measured in hours, hospital admission and subsequent length of stay, incidence of MACE occurring within 30 days of ED attendance, comparative costs, participant satisfaction (quantitative survey) and acceptability to patients (qualitative methodology).

### Follow-up processes

#### Participants with an hs-troponin at presentation below the LoD

All participants with an initial hs-troponin below the LoD (irrespective of group allocation) will be followed up by telephone by the research nurse, or by email, at 30 (+5) days after index presentation to capture information about any adverse events and any primary care or secondary care health service use since discharge from the ED.

If the participant indicates that they have attended any health service provider for any reason since discharge from the ED, but there is concern over patient recall of events, then research nurses will review hospital records (where available) to verify outcomes.

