## Methods and analysis

### Study design and conduct

This is a pragmatic, multicentre, randomised controlled parallel group trial in adult patients presenting to the ED with suspected cardiac chest pain and who trigger the chest pain investigation pathway. Five hundred and ninety-four participants will be randomised in a 1:1 ratio to be managed according to the LoDED strategy (allowing discharge after a single hs-troponin test at presentation to ED if a participant has no new ischaemic ECG changes and the hs-troponin is below the LoD) or the usual care rule-out strategy in current clinical use at each study site. Usual care will usually include two hs-troponin blood tests taken between 1 and 6 hours after presentation and may vary between sites.

This is an open study. Participants’ study allocations will only be blinded to those performing central review of data for the assessment of outcomes and the statistician analysing the results. All patients will be consented and randomised before their initial hs-troponin results are known. Patients will be ineligible to participate in the trial once the initial hs-troponin result is known to the treating clinician in order to prevent selection bias. The decision to discharge a patient will be made after clinical assessment by the treating clinician. In the event of ongoing clinical concern, the clinician may proceed with further testing and/or admission at their discretion, and contrary to the allocated strategy. Information on protocol adherence will be collected to facilitate a per-protocol analysis as well as the primary intention-to-treat analysis.

The key objective of this study is to conduct a randomised controlled trial (RCT) of the LoDED strategy versus usual care to compare the proportion of patients successfully discharged within 4 hours of arrival, with no MACE during the following 30 days. We will also measure admission rates, hospital bed usage, length of stay, resource use and patient satisfaction, facilitating a health economic evaluation, and determine whether the LoDED strategy is acceptable to patients through qualitative interviews.

Day-to-day trial management is administered through the UKCRC-registered Peninsula Clinical Trials Unit (CTU) at Plymouth University and sponsored by North Bristol NHS Trust.

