#### Outcome adjudication

Incidence of MACE occurring within 30 days of ED attendance will be recorded on a serious adverse event (SAE) form by the local principal investigator or designee with reference to relevant clinical information and responses to 30-day follow-up telephone assessments uploaded to the study database. All participant data will be reviewed by an independent adjudication committee at the end of the study to confirm the primary outcome.

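### For below-LoD participants who report an attendance, record review depends on doubt about recall, so a post-discharge AMI can be missed without its troponin values being seen

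*Protocol article*

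**What the plan says.** All references are to the protocol article.

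- **Follow-up, below-LoD participants.** In both arms they are contacted once: "irrespective of group allocation) will be followed up by telephone by the research nurse, or by email, at 30 (+5) days" after presentation. If they report having attended any provider, "but there is concern over patient recall of events, then research nurses will review hospital records (where available) to verify outcomes". The article gives no criterion for that concern.
- **Follow-up, remaining participants.** Those above the LoD get a screening text. Anyone who answers yes or does not respond is telephoned, or has routine data taken from local hospital electronic records. Doubt about recall plays no part in that trigger.
- **Primary outcome.** Success is "discharge from hospital within 4 hours of ED arrival, without MACE occurring within 30 days". For AMI, "a rise and/or fall of troponin above the 99th percentile value confirms the diagnosis", and the change must be "an absolute change in troponin over time of at least half the 99th percentile value of the assay in clinical use".
- **Study design and conduct.** The trial is open: "Participants’ study allocations will only be blinded to those performing central review of data for the assessment of outcomes and the statistician analysing the results".
- **Outcome adjudication.** MACE is entered on an SAE form by the local principal investigator or a designee "with reference to relevant clinical information and responses to 30-day follow-up telephone assessments uploaded to the study database". An independent committee reviews all participant data at the end of the study.
- **Safety and data monitoring.** Suspected SAEs are reported within 24 hours of discovery, and those considered MACE are adjudicated.

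**The concern.** Recall quality is the wrong trigger for an endpoint defined by laboratory values. A participant may remember a re-attendance perfectly and still not know whether troponin rose by half the 99th percentile. Under the stated rule, the more confident the account, the less likely the record is to be opened.

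Two consequences follow. First, a post-discharge AMI that neither the participant nor the site recognises as a cardiac event can be recorded as no MACE. Second, the decision to look further is a judgement that appears to fall to the research nurses who make the calls and review the records. They are not among those listed as blinded, so knowledge of the allocation could influence which reports are checked.

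What is at stake is mainly the 30-day MACE result in the patients whom LoDED allows to leave after one blood test. MACE is also a component of the primary outcome.

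**Working it through.** **1. The plan's own figure.** Inputs from *Sample size*: 8% v 17%, 90% power, 5% significance (taken as two-sided), 95% follow-up. With pooled variance and no continuity correction:

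n = [1.960 × √(2 × 0.125 × 0.875) + 1.2816 × √(0.08 × 0.92 + 0.17 × 0.83)]² / 0.09² = (0.917 + 0.594)² / 0.0081 ≈ 281.7, so 282 per group and 564 in total. Then 564 / 0.95 = 593.7, so 594.

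The stated numbers reproduce, and this point does not alter them.

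**2. Path of a reported attendance (below LoD).**

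| Situation | What the article provides |
|---|---|
| Event suspected to be an SAE or MACE | SAE form with clinical information, then adjudication |
| Not suspected, recall doubted | Record review, where records are available |
| Not suspected, recall not doubted | No record review required |
| AMI at the index visit | Troponin taken from the laboratory system (*Baseline blood sampling*) |

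Only the third row is exposed. The committee reviews all data, but for that row the troponin values need not be among the data.

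**3. How many participants and reports.** The planning range below the LoD is 10%-60% (*Sample size*): 594 × 0.10 = 59 and 594 × 0.60 = 356. The assay-specific shares in the *Introduction* are 25%-34%: 594 × 0.25 = 149 and 594 × 0.34 = 202. The article gives no attendance rate; 10%-30% is assumed.

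- Planning range: 59.4 × 0.10 = 6 to 356.4 × 0.30 = 107 reports.
- Assay-specific range: 148.5 × 0.10 = 15 to 202.0 × 0.30 = 61 reports.

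**4. Effect on the primary comparison.** Suppose a fraction m (assumed) of the 17% discharged early on LoDED had MACE. Counting every such case as a failure gives success = 0.17 × (1 − m) and 0.17 × 297 × m patients affected. Power is at 282 per group against 8%.

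| m | Patients per 297 | Success | Power |
|---|---|---|---|
| 0 | 0 | 17.0% | 90.0% |
| 0.5% | 0.3 | 16.9% | 89.6% |
| 1% | 0.5 | 16.8% | 89.1% |
| 2% | 1.0 | 16.7% | 88.1% |
| 5% | 2.5 | 16.2% | 84.6% |

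Missing all of these events would overstate LoDED success by 0.3 percentage points at m = 2% (17.0 − 16.7).

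**5. Effect on the safety result.** About 0.17 × 297 = 50 LoDED participants are expected to leave within 4 hours, so one event among them is 1/50 = 2%.

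For the expected number of MACE below the LoD, the *Introduction* gives a pooled sensitivity of 98.0% (95% CI 94.7% to 99.3%) for hs-troponin T. With MACE assumed in 5%-10% of participants, 594 × 0.05 × 0.02 = 0.6 to 594 × 0.10 × 0.02 = 1.2. At the confidence limits the range is 594 × 0.05 × 0.007 = 0.2 to 594 × 0.10 × 0.053 = 3.1. These counts pool both arms and include index-visit events, so the number exposed to the recall rule is smaller.

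**The case against.** The strongest reply is that the recall check is an extra step and not the whole of ascertainment. The 30-day contact asks about any adverse event. A suspected MACE goes onto an SAE form completed with clinical information, is followed up and is adjudicated by blinded reviewers. This stands, and it disposes of one tempting inference: that an AMI could be ruled in on self-report alone. The article does not allow that. The remaining gap is an event that nobody suspects.

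A reader might also infer that the arms will be verified unequally. The article does not say so: one rule applies whatever the allocation. It also does not state who judges recall; that research nurses do so is an inference from their making the calls and reviewing the records. Uneven checking is therefore only a risk arising from discretion in an open trial.

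The weak basis for the magnitude is a fair criticism too. The attendance and MACE rates are assumptions, and the MACE counts include index events that do not depend on recall.

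Finally, it can be said that an article leaves operational criteria to the full protocol. That covers the missing definition of concern, but not the choice of recall as the trigger, which the article states and which does not match its own AMI definition.

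**Conclusion.** The point holds as a limited weakness in how post-discharge MACE is ascertained below the LoD. A confidently recalled re-attendance that is not flagged as a suspected SAE can be classified as no MACE with its troponin values unseen, and blinded central review cannot repair that.

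The primary comparison is little affected: power stays at or above 88.1% for assumed MACE rates up to 2% among early LoDED discharges, and is 84.6% at 5%. The 30-day MACE result is more sensitive, because one event among about 50 early discharges is 2%. It would go too far to say that one unverified report could be the whole safety signal: the expected counts of 0.6-1.2 rest on assumed rates, pool both arms and include index-visit events. Index-visit AMI and the sample size are not affected. The change is worth making because it is specific and inexpensive.

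**What to change.** Replace the recall trigger with an objective one. For every below-LoD participant, in either arm, who reports an emergency department or hospital attendance within 30 days, review the available hospital record (diagnosis, troponin values, ECG, procedures) and pass it to the blinded adjudication committee. Where the record cannot be obtained, report the number by arm.

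The cost is research-nurse time, through a record-review route that the protocol already uses for both follow-up groups. At an assumed attendance rate of 10%-30%, this is about 6-107 checks over the planned 10%-60% below the LoD, or about 15-61 at 25%-34%. Attendances at hospitals whose records the site cannot see will remain unverified, which is why their number should be reported.

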#### Remaining participants

Participants with an initial hs-troponin above the LoD will be sent a screening text message after 30 (+5) days by the study team. This text will ask: ‘Since you came to the Emergency Department with chest pain have you needed to see your GP or re-attend an Emergency Department or visit an outpatient clinic for assessment of chest pain?’ Patients answering ‘No’ will require no further follow-up. Participants who fail to respond, or answer ‘Yes’, will be followed up by telephone by the research nurse or routine data will be collected from local hospital electronic patient records on initial diagnosis, local reattendance and outpatient follow-up.

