### Sample size

Current observational research gives estimates of the proportion of patients with an hs-troponin <LoD in the intervention group of the RCT (LoDED strategy) of between 10% and 60%.^11–17^ UK observational data suggest that these patients will be discharged within a median time of 3.5 hours (taking into account laboratory processing and 60 min of decision-making time).^10^ Data provided to us from a recent pragmatic RCT evaluating a 0/2-hour hs-troponin rule-out strategy have demonstrated that only 10% of patients will be discharged within 4 hours using this approach.^9^ Clinical protocols using rule-out strategies at later time points (eg, 3 hours) will be expected to have even fewer patients discharged within the 4-hour time frame; similarly the 0/1-hour strategy may realise a marginal increase in discharges before 4 hours. These differences have been taken into account within the power calculation. For the overall population we anticipate 8% will be discharged within 4 hours using usual care and at least 17% using the LoDED strategy. Therefore, this study will be powered to detect a 9% difference between the early discharge rates with 90% power and 5% statistical significance. This will require 282 patients in each group and 564 patients in total with primary outcome data. Assuming a 95% follow-up rate, 594 patients need to be recruited. Recruitment will take place over a 9-month period.

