### Health economic analysis

The primary economic analysis will include all randomised participants (intention-to-diagnose analysis) and compare secondary care costs. Secondary care resource use will be valued using national sources of unit costs. A subgroup analysis will provide extra detail on the primary and community care costs (in addition to the secondary care costs) and consequences (quality-adjusted life-years (QALY)) for any participant with an hs-troponin below the LoD. This applies to both trial groups. Data collection for the additional primary and community care costs will be based on participant self-report following administration of a structured resource use questionnaire at 30 days and standard methods of unit costing. QALYs will be derived from the EQ-5D (5-level version) using the set of preference weights recommended by NICE at the time of analysis.^24^

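### Above the LoD, a 'No' to a text that does not ask about admission, heart attack or revascularisation ends 30-day follow-up, so some post-discharge MACE may be missed

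*Protocol article*

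**What the plan says.** The Primary outcome section defines MACE as "cardiac death, AMI or emergency revascularisation occurring within 30 days of ED attendance", with the index presentation included. It is part of the primary outcome and also a listed secondary outcome.

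Thirty-day follow-up then depends on the first hs-troponin.

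- **Below the LoD.** Everyone is contacted by telephone or email about adverse events and "any primary care or secondary care health service use since discharge from the ED". Hospital records are reviewed if recall is in doubt.
- **Above the LoD** (section Remaining participants). A screening text asks whether the participant has needed to see a GP or "re-attend an Emergency Department or visit an outpatient clinic for assessment of chest pain". The closing rule is "Patients answering ‘No’ will require no further follow-up". Those who answer 'Yes' or do not reply are telephoned, or data are taken from local hospital records.

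Under Outcome adjudication, the local investigator records MACE on an SAE form from clinical information and 30-day telephone responses, and an independent committee reviews all participants at the end. The Data analysis section reports MACE with 95% CIs for participants discharged under the LoDED strategy against usual care, and expects few events.

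**The concern.** The question put to participants does not match the outcome it is meant to screen for. MACE consists of cardiac death, AMI and emergency revascularisation; the text asks about three kinds of visit. A direct admission, a transfer, or an infarction that presented without chest pain could truthfully be answered 'No', after which nothing further is scheduled.

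The wording is also ambiguous. The closing reference to chest pain may qualify all three visits or only the outpatient one, so two participants with the same history could answer differently. Admission, heart attack and revascularisation are not asked about on either reading.

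The more searching enquiry goes to the group at lower risk. At stake is the secondary 30-day MACE incidence, where a few lost events matter because few are expected. Adjudicators can confirm only what has been collected, and 'No' repliers have no telephone assessment to draw on.

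**Working it through.** **1. The plan's own figure.** The Sample size section states that "we anticipate 8% will be discharged within 4 hours using usual care and at least 17% using the LoDED strategy", with 90% power at 5% significance. Taking the test as two-sided, with pooled variance and no continuity correction:

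- mean rate = (0.08 + 0.17)/2 = 0.125
- n = [1.960 × √(2 × 0.125 × 0.875) + 1.2816 × √(0.08 × 0.92 + 0.17 × 0.83)]² / 0.09² = 281.7, so 282 per group and 564 in total
- 564/0.95 = 593.7, so 594

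Both stated figures reproduce, and power at 282 per group is 90.0%. The sample size is not in dispute.

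**2. How many take the text route.** The Introduction gives about 30% eligible for early discharge with hs-troponin T, and the Sample size section gives 10% to 60% below the LoD.

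- At 30%: 594 × 0.70 = 416
- At 60% and 10%: 594 × 0.40 = 238 and 594 × 0.90 = 535

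**3. How many events could be lost.** Only post-discharge MACE in above-LoD participants who answer 'No' is exposed:

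missed = 594 × MACE rate × share above the LoD × share arising after discharge × share of those missed

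- *Share above the LoD:* 0.98, from the pooled sensitivities of 98.0% and 97.9% in the Introduction. These come from outside cohorts and describe LoD plus ECG, so this is an approximation.
- *MACE rate:* not stated; assumed 2% to 10%, because the Introduction says 90% have a benign cause.
- *Share after discharge:* not stated; assumed 5% to 20%.
- *Share of those missed:* not stated; assumed 10% to 50%.

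| Case | Calculation | Events missed | Share of all MACE |
|---|---|---|---|
| Low | 594 × 0.02 × 0.98 × 0.05 × 0.10 | 0.06 | 0.5% |
| Middle | 594 × 0.05 × 0.98 × 0.10 × 0.25 | 0.73 | 2.5% |
| High | 594 × 0.10 × 0.98 × 0.20 × 0.50 | 5.8 | 9.8% |

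With the lower confidence limit of 94.7% for the share above the LoD, the high case is 594 × 0.10 × 0.947 × 0.20 × 0.50 = 5.6. The share after discharge matters more: at 50%, the high case becomes 594 × 0.10 × 0.98 × 0.50 × 0.50 = 14.6, or 24.5% of all MACE.

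**4. Effect on the primary outcome.** A missed MACE matters here only if the participant was discharged within 4 hours. As an extreme case, suppose every early discharge is above the LoD, 2% have later MACE (assumed), and all are missed.

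- Control overstated by 0.08 × 0.02 = 0.16 points
- LoDED overstated by 0.17 × 0.02 = 0.34 points
- Difference overstated by 0.34 − 0.16 = 0.18 points
- Power at the corrected rates (7.84% and 16.66%) is 89.4%, against 90.0%

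**5. The reported MACE comparison.** Read literally, participants discharged under the LoDED strategy are all below the LoD, so all have telephone or email contact. The usual-care side includes above-LoD participants closed by text. The two sides would then be ascertained differently, and lost events would fall on the usual-care side. If the report is by randomised arm, the same rule applies in both arms and both incidences are lowered.

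**The case against.** Much of the case for leaving the rule alone is sound.

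- **Nearly all MACE lies above the LoD, so a reader might infer that about 98% of events depend on the text.** They do not. MACE includes the index presentation, and above-LoD participants in the intervention arm revert to the local rule-out strategy, usually with serial troponin, as in control. Index events are seen in hospital. Ischaemic ECGs are excluded as well, so the above-LoD share in this trial may be below 98%.
- **Other routes exist.** Non-responders, who would include participants who died, go to telephone or records. SAE reporting applies to everyone. This stands, but a later event in a 'No' replier reaches an SAE form only if the site learns of it some other way.
- **Chest-pain-only is one reading.** On the other, any GP visit or ED re-attendance prompts a 'Yes', and the gap is smaller.
- **The tiers have a rationale.** The two strategies differ only below the LoD, where both arms get full contact. Because follow-up is set by troponin and not by arm, no differential loss is built into the randomised contrast.
- **A reader might also infer that secondary care costs are lost.** The Health economic analysis section says "The primary economic analysis will include all randomised participants (intention-to-diagnose analysis) and compare secondary care costs", but nowhere makes the text the source of those costs, so the inference is not supported.
- **The protocol does not say that a 'No' is coded as MACE-free.** It says only that follow-up stops. It also names no further check before such a participant is counted.

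These points limit the size of the problem. They do not make the text capable of excluding the events in the MACE definition.

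**Conclusion.** The point holds as a limited weakness in ascertainment of a secondary safety outcome. A 'No' ends scheduled follow-up without asking about admission, heart attack or revascularisation, so post-discharge MACE in those participants may be missed. Under-counting is a risk, not something the protocol demonstrates. Its size cannot be computed from the document: about 0 to 6 of 594 under the assumed rates, and more only if a much larger share of events arises after discharge.

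The secondary 30-day MACE incidence and its CI are exposed, most clearly if the comparison is made literally between participants discharged under the LoDED strategy and usual care. The primary outcome and the power of the trial are not materially affected. It is worth correcting because the correction is cheap.

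**What to change.** 1. In Remaining participants, reword the text to ask whether, since the index visit and for any reason, the participant has attended any hospital or ED, been admitted, been told of a heart attack, or had a coronary procedure. Any 'Yes' then triggers the telephone or record follow-up already planned.
2. Where feasible, extend the local record check that is already an option for 'Yes' repliers and non-responders to 'No' repliers, before they are counted as MACE-free.

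The first step needs a minor amendment to a message already being sent. Recruitment began on 4 June 2018, so ascertainment will be mixed before and after the change; recording which wording each participant received lets this be reported. The second step takes some staff time for at most the number on the text route (416 if 30% are below the LoD), fewer in practice because it concerns only 'No' repliers. Local records miss care given elsewhere, so the check supplements the reworded question and does not replace it.
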